## **2. Quantitative Analysis Plan**

This plan covers any quantitative analyses for the feasibility trial. The trial will also undertake some qualitative research which will not be covered in this plan.

### **2.1 Overview**

This feasibility trial will estimate parameters needed for planning an efficacy trial including various rates (e.g. recruitment, randomisation, losses to follow-up) and the within-trial arm means and standard deviations for possible outcome measures to inform the sample size calculation of a future randomised controlled trial. Scores for published questionnaires will be summarised for each measure, and outcome measures will be described by trial arm. Intervention effect sizes (e.g. mean differences for continuous outcome measures at follow-up between arms) will be estimated for all secondary outcome measures as previously described, but no formal hypothesis testing will be carried out. All analyses will be based on the modified intention-to-treat principle. The final statistical report will be produced according to KCTU SOP ST-07 (Statistical Reports, V3.0).

### **2.2 Recruitment and representativeness of recruited patients**

In addition to the participation outcomes listed in section 1.9.1, we will require the following information to construct the CONSORT flowchart (see template flowchart in Figure 1):

- Number of potentially eligible participants completing pre-screening questionnaire
- Number of participants deemed ineligible, and reasons why
- Number of participants withdrawing and/or lost to follow-up between pre-screening and baseline home assessments
- Number of participants continuing through trial
- Number of participants withdrawing and reasons why
- Number of participants excluded from analysis and reasons why

The representativeness of recruited patients will be shown through descriptive summaries of socio-economic/demographic data.

The trial will be reported according to the CONSORT extension guidelines for pilot trials [3].

**Figure 1. Template CONSORT diagram for PASTI feasibility trial**

[figure not shown]

### **2.3 Description of sample characteristics at baseline**

To describe the study sample and check that the trial arms are balanced, demographic and baseline variables will be summarised by trial arm and across the total study sample. Summary statistics will be calculated (means and standard deviations [SDs] for continuous outcomes if normally distributed, medians and quartiles if skewed; frequencies and proportions for discrete outcomes). The randomisation of intervention groups to participants should have ensured that any imbalance over all measured and unmeasured baseline characteristics is due to chance. Therefore, no significance testing will be conducted to assess evidence of group differences for these baseline variables.

### **2.4 Estimation of feasibility parameters**

In addition to drafting the CONSORT participant flowchart, the following details will be reported along with appropriate 95% confidence intervals (CIs):

#### **1. Participation rate:**

- Number and proportion of participants consenting to the full trial out of those eligible and invited to take part.
- Distribution of socioeconomic profiles for families enrolled relative to geographic norms (e.g. Central/Greater London)

The number and proportion of randomised participants out of those deemed eligible and were invited to take part will also be reported.

#### **2. Intervention adherence (in the PASTI arm):**

- Average proportion of parents that reported no screen time in the hour before bed during the intervention period
  - First, the proportion of 'no screen time' reported out of the number of daily adherence questionnaires completed will be calculated for each PASTI arm participant. Then, this proportion will be averaged across all participants randomised to PASTI

#### **3. Participant retention:**

- Number and proportion of participants attending the follow-up lab visit out of those randomised overall and by trial arm
- Number and proportion of participants that complete all follow-up outcome home and lab assessments out of those randomised overall and by trial arm

#### **4. Parent experiences (in the PASTI arm):**

- Frequency and proportion of parent experience ratings from debrief survey completed by PASTI arm participants

#### **5. Assessment acceptability (in the PASTI arm):**

- Frequency and proportion of parent study assessment acceptability ratings from debrief survey completed by PASTI arm participants

The distribution of parent experience ratings and study assessment acceptability ratings from debrief surveys completed by Bedtime Box arm participants will also be summarised.

We have chosen to implement a 'traffic light' system to assess the feasibility of a full-scale PASTI trial. Performance metrics that fall in the Red zone

indicate that a full trial following the current design may not be feasible, metrics that fall in the Amber zone indicate that a full trial may be feasible but the protocol should be modified or the situation monitored closely, and metrics that fall in the Green zone indicate that a full trial is feasible and we may continue without substantial modifications to the current study design.

| Metric                                                                                                                                                                                         | Red zone | Amber zone | Green zone |
|------------------------------------------------------------------------------------------------------------------------------------------------------------------------------------------------|----------|------------|------------|
| Randomisation
(Number of participants randomised overall)                                                                                                                            | ≤ 73     | 74 to 104  | ≥ 105      |
| PASTI daily questionnaire completion
(% of participants randomised to PASTI and retained to lab follow-up that complete ≥ 60% of daily screen time questionnaires)                   | < 65%    | 65% to 79% | ≥ 80%      |
| PASTI adherence to screen time removal (week 1 – week 6)
(% of participants randomised to PASTI that report no screen time on ≥ 60% of daily screen time questionnaires completed)   | < 50%    | 50% to 69% | ≥ 70%      |
| PASTI debrief questionnaire completion
(% of participants randomised to PASTI that complete the debrief questionnaire measuring participant experience and assessment acceptability) | < 65%    | 65% to 74% | ≥ 75%      |
| Retention
(% of randomised participants attending follow-up Lab visit)                                                                                                               | < 70%    | 70% to 74% | ≥ 75%      |

## **2.5 Description of follow-up outcome measures**

Follow-up outcome measures (see Appendix for details) will be summarised by trial arm and for the total sample using descriptive statistics.

## **2.6 Secondary outcomes**

### **2.6.1 Descriptive analysis**

The secondary outcomes listed in Section 1.9.2 will be summarised using descriptive statistics at baseline and follow-up timepoints.

### **2.6.2 Treatment Effects**

#### **2.6.2.1 Continuous outcome data**

Outcomes will be analysed with crude and an adjusted multivariable linear regression analysis. Fixed effects included will be: dummy treatment variables; baseline values of continuous outcomes; minimisation factors (child age group, child sex, family IMD quintile).

The treatment group mean difference (MD) for unstandardised effect sizes and 95% confidence intervals will be presented for both crude and adjusted estimates. Given the sample size and purpose of this feasibility trial, these estimates will not be the basis for inferential statements and p-values will not be reported. The purpose of our effect size estimates is to illustrate the size of effects across a number of possible outcomes.

#### **2.6.2.2 Binary outcome data**

Any binary outcomes will be analysed with crude and an adjusted multivariable logistic regression analysis. Fixed effects will include the baseline values of binary outcomes; minimisation factors (child age group, child sex, family IMD quintile). Summary effects will be reported as crude odds ratio and adjusted odds ratio (aOR) with 95% CI. No p-values will be reported.

#### **2.6.2.3 Count outcome data**

Frequency of night awakenings is likely to be a highly skewed count variable (measured as the average number of night awakenings over the week-long actigraphy period). The distribution of night awakenings will be examined to determine which zero-inflated regression model would be most appropriate (i.e. if count data is overdispersed, a negative binomial model may be used instead of a Poisson regression model). Incidence rate ratios (IRRs) will be reported with 95% CIs. No p-values will be reported.

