## 1.8 Sample size estimation (including clinical significance)

In line with guidance on feasibility studies, no power calculation has been carried out [1]. A sample size of 60 to 100 has been shown to be sufficient in a feasibility trial [2]. A target sample size of 105 (N=35/arm) will be enrolled and randomised.

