### 1.9.2 Secondary outcomes:

We will estimate preliminary PASTI effect sizes on the following outcomes at the Weeks 6-7 follow-up home and lab visits:

1. Total infant night-time sleep duration (minutes) using actigraphy (averaged across the 7-9 day actigraphy period immediately preceding the lab visit)
2. Exogenous attention control (single search saccadic reaction time from the Visual Search Task)
3. Average toddler screen use (minutes) in the hour before bed (measured using responses from one weekday and one weekend bedtime activity diary directly preceding the lab visits and with the following formula:  $[\text{average weekday screentime} * 5] + [\text{average weekend screentime} * 2] / 7$ )
4. Additional sleep outcomes:
  - a. Average day-time nap duration (minutes) using actigraphy
  - b. Frequency of night awakenings using actigraphy (averaged across the 7-9 day actigraphy period immediately preceding the lab visit)
  - c. Sleep efficiency (total night time sleep duration expressed as a percentage of time in bed, averaged across the 7-9 day actigraphy period immediately preceding the lab visit) using actigraphy
  - d. Parent-reported sleep onset latency (minutes) from the BISQ-R
5. Additional attention control outcomes (reaction times in milliseconds):
  - a. Prosaccade saccadic reaction time from the Antisaccade Task
  - b. Proportion of antisaccades from the Antisaccade Task
  - c. Baseline saccadic reaction time from the Gap-Overlap Task
  - d. Disengagement saccadic reaction time from the Gap-Overlap Task
  - e. Parent-reported inhibitory control subscale score from the ECBQ
  - f. Parent-reported effortful control global score from the ECBQ

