## **2.9 *Pre-processing of actigraphy and eye-tracking data***

### **2.9.1 Actigraphy data**

Pre-processing of Actigraphy data will be done in the CamNtech MotionWare Software. The following data will be excluded before analysis:

- Periods of non-wear will be excluded using the MotionWare algorithm and parent-reported Actigraph removal on the Sleep Diary.
- Periods of external movement (e.g. car/buggy) will be excluded using the parent-reported Sleep Diary.

Actigraphy sleep analysis will be conducted using the CamNtech MotionWare software to deduce our primary and secondary sleep metrics. Daytime nap data will be excluded if any of the following are observed:

- A period of non-wear was reported during the nap period
- A period of external movement was reported during the nap period
- The parent reported that the child's day was not typical (e.g. child illness, child sleeping in different location, disturbance) using the parent-reported Sleep Diary.

Night time sleep data will be excluded if any of the following are observed:

- A period of non-wear was reported during the sleep period
- A period of external movement was reported during the sleep period
- The parent reported that the child's night was not typical (e.g. child illness, child sleeping in different location, disturbance) using the parent-reported Sleep Diary.
- The sleep period occurred on Daylight Saving Time (e.g. 30/10/2022)

Actigraph data for each participant will be excluded from all analysis if there are < 3 days day or night data, respectively for nap or sleep analysis.

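### Night awakenings are defined as a per-night average but are to be fitted with a zero-inflated count model that has no exposure term, so the interval for the rate ratio can be too wide or too narrow (should-fix)

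*SAP*

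**What the plan says.** Section 1.9.2, item 4b, lists the outcome as "Frequency of night awakenings using actigraphy (averaged across the 7-9 day actigraphy period immediately preceding the lab visit"). Section 2.6.2.3 calls it a highly skewed count variable and in the same sentence describes it as "measured as the average number of night awakenings over the week-long actigraphy period".

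On the model, section 2.6.2.3 says "The distribution of night awakenings will be examined to determine which zero-inflated regression model would be most appropriate", and explains in brackets that "if count data is overdispersed, a negative binomial model may be used instead of a Poisson regression model". Read literally, zero inflation is settled and only the choice between Poisson and negative binomial is open. On reporting: "Incidence rate ratios (IRRs) will be reported with 95% CIs", and "No p-values will be reported".

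The section names no offset or exposure for the number of nights, no robust standard error, no content for the inflation part of the model, and no covariates. Section 2.6.2.1, by contrast, lists treatment dummies, baseline values and minimisation factors.

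The number of nights behind each average varies. Section 2.9.1 removes nights with non-wear, external movement, an atypical night or a clock change, and then sets the floor: "Actigraph data for each participant will be excluded from all analysis if there are < 3 days day or night data". With a 7-9 day recording period, a child's average can rest on anything from 3 to 9 nights. The sample size in section 1.8 is "A target sample size of 105 (N=35/arm) will be enrolled and randomised".

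**The concern.** An average over several nights is not a count. Most of its values are not integers, and its night-to-night variance is smaller than that of a single night by roughly the number of nights averaged. A Poisson model sets the variance equal to the mean, and a negative binomial model sets it at or above the mean. Both are statements about one night's count, so applied to the average they use the wrong variance and give no more weight to a child with 9 nights than to one with 3.

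Fixing zero inflation in advance raises a second problem. An average is zero only if every valid night was free of awakenings, so a surplus of zeros should be shown before it is modelled. If a zero class is material and its size differs by arm, the ratio from the count part describes only the children outside that class.

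With no p-values, the IRR and its 95% CI are the whole between-arm result for this outcome. An interval of the wrong width, or a ratio of unclear meaning, defeats the purpose of illustrating the size of the effect.

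**Working it through.** The SAP states no awakening rate, dispersion or power figure for this outcome, so there is no figure of its own to reproduce.

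**Inputs.** From the SAP: 35 per arm; 7-9 nights recorded; at least 3 valid nights. Assumed: mean awakenings per night μ from 0.5 to 10; between-child gamma dispersion k from 0 to 1 (k is the squared coefficient of variation of children's true rates); Poisson variation from night to night; no true effect; two arms compared; no covariates. m is the number of valid nights.

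**Step 1: support.** In simulation, 79 to 87% of the averages were not integers.

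**Step 2: variance.** The true variance of a child's average is μ/m + kμ². Poisson on the average assumes μ. For the log ratio with n per arm:

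- model SE = √(2/(nμ))
- true SD ≈ √((2/n)(1/(mμ) + k))

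At μ = 1, k = 0, m = 7: model SE = √(2/35) = 0.239; true SD = √((2/35)/7) = 0.090; ratio √7 = 2.6, so the interval is far too wide.

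At μ = 10, k = 0.3, m = 7: model SE = √(2/350) = 0.076; true SD = √((2/35)(1/70 + 0.3)) = 0.134; ratio 0.56, so the interval is too narrow. The implied coverage is P(|Z| < 1.96 × 0.56), about 73%.

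**Step 3: what negative binomial can repair.** Its variance is the mean plus a non-negative term. It cannot match μ/m + kμ² when that is below μ, that is, when kμ < 1 − 1/m. With m = 7 the bound is 0.86. Below it, negative binomial falls back to Poisson and stays too wide; above it, the extra term can absorb the excess.

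**Step 4: simulated coverage of the 95% CI.** Seven nights, 35 per arm, models fitted to the averages with model-based SEs. The negative binomial was fitted without an inflation part.

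| μ | k | kμ | Zero-inflated Poisson | Negative binomial |
|---|---|---|---|---|
| 1 | 0 | 0 | 99.7% (SE 0.239, SD 0.087) | 100% |
| 1 | 0.3 | 0.3 | 99.0% (SE 0.237, SD 0.157) | 99.5% |
| 2 | 0.3 | 0.6 | 97.2% | 98.2% |
| 1 | 1 | 1.0 | 91.8% | 94.0% |
| 10 | 0.1 | 1.0 | 91.4% | 95.0% |
| 10 | 0.3 | 3.0 | 73.9% (SE 0.074, SD 0.128) | 94.5% |

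A separate simulation with 3 to 9 nights per child agrees. Zero-inflated Poisson covered nearly 100% at μ = 1, k = 0 (SE 0.239 against SD 0.101, ratio 2.4) and 71% at μ = 10, k = 0.3.

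Total awakenings with log(valid nights) as offset and robust SEs covered 93 to 95% in the first set and 90 to 95% in the second. Poisson on the average with robust SEs covered 93 to 95%. At μ = 1 over 7 nights, the CI for the log ratio is 0.35 wide (k = 0) or 0.61 (k = 0.3) with the offset model, against about 0.94 for Poisson on the averages.

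**Step 5: zeros.** P(average = 0) is exp(−μm) for k = 0 and (1 + kμm)^(−1/k) otherwise.

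| μ | k | 3 nights | 7 nights |
|---|---|---|---|
| 1 | 0 | 5.0% | 0.09% |
| 1 | 0.3 | 11.8% | 2.3% |
| 2 | 0.3 | 3.2% | 0.4% |
| 1 | 1 | 25% | 12.5% |
| 0.5 | 1 | 40% | 22% |

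The larger shares arise from low rates, few nights and strong ordinary variation between children, not from a separate always-zero class. In the six zero-inflated Poisson scenarios of step 4 the median fitted inflation probability was about 0.

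**Step 6: meaning of the IRR.** Suppose always-zero shares of 20% and 40% and a ratio of 1.0 among the other children. The ratio of arm means is (1 − 0.4)/(1 − 0.2) = 0.75. On simulated integer counts, the zero-inflated IRR was 1.00 with treatment in the inflation part and 0.88 with a constant inflation part. With equal shares of 20%, it agreed with the ratio of arm means (0.79 against 0.80).

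**The case against.** The strongest defence is about consequence. Night awakenings are one of four additional sleep outcomes. Section 1.1.1 names night-time sleep duration and singleton-search reaction time as the outcomes whose parameters will power the later trial, and no traffic-light metric in section 2.4 uses awakenings. The means and SDs for planning are descriptive and do not depend on this model. All of that stands, and it limits the severity.

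Second, section 2.6.2.3 already offers negative binomial under overdispersion, and this largely repairs the too-narrow case (94.5% at mean 10, k = 0.3). That also stands, with two limits: the wording is only that it may be used, and it does nothing for the too-wide case.

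Third, the bracketed clause could be read as an ordinary choice between Poisson and negative binomial. The sentence around it nevertheless says zero-inflated.

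Two stronger readings are tempting. A reader might infer that the intervals will always be wrong. The figures do not support this: the error has no fixed direction, and some settings are near nominal. A reader might also infer that the IRR necessarily describes a latent subgroup. If zeros are rare, the inflation part vanishes and the IRR is the ordinary ratio of means; the two part only when zero inflation is material and differs by arm.

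The missing covariate list is a drafting gap and is no evidence about the likelihood.

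**Conclusion.** The point holds as a should-fix. The SAP defines an average per night over a varying number of nights and then prescribes a count model that ignores that number.

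Under the assumed rates, the interval is too wide when awakenings are few (SE about 2.4 times the true SD with 3 to 9 nights, 2.7 times with exactly 7; coverage near 100%). If Poisson is kept, it is too narrow when awakenings are many and vary between children (coverage 71 to 74% at mean 10, k = 0.3). Negative binomial largely cures the second fault but not the first. Which case applies cannot be told from the SAP, because it gives no awakening rate or dispersion.

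All-zero averages are uncommon unless rates are low and vary strongly between children, or few nights are valid, so the document gives no ground for fixing zero inflation in advance.

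The results rest on a gamma-Poisson model without covariates, and zero-inflated negative binomial was not simulated. It would be wrong to conclude that any feasibility decision or the sample size of the later trial depends on this: the outcome feeds neither, and no test is planned.

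**What to change.** Reword section 2.6.2.3 before database lock:

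- Analyse each child's total awakenings over observed valid nights with log(number of valid nights) as offset, using negative binomial or Poisson regression with robust SEs.
- Include the treatment dummies, the baseline awakening rate and the minimisation factors, as in section 2.6.2.1, and report crude and adjusted ratios.
- Add zero inflation only if the data clearly need it. In that case state what enters the inflation part and report the marginal ratio of arm means.
- Count only observed nights in the total and the offset. Nights filled in by the prorating in section 2.8.3 would add exposure that was not observed.
- If only averages can be exported, fit a log-link quasi-likelihood model to the average with robust SEs.

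The cost is a change of wording and some extra data handling to export totals and valid nights. The SAP does not say that these are already in the export (Appendix 1 lists only awakening frequency), so this should be checked with the team processing the actigraphy data. No new data collection is needed.

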### **2.8.3 Missing items in lab and actigraphy measures**

During baseline and follow-up home assessments, parents will be asked to fit actigraphy watches to their infant's ankle over a 7-9 day period. If data from actigraphy watches is missing, we may prorate if data is available from 70% of the home assessment period (i.e. if data on total infant night-time sleep duration is available from 7 out of 9 days, replace missing item values with the average value of the complete items for each individual).

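### Night awakenings are defined as a per-night average but assigned a zero-inflated count model, so the plan's overdispersion check is unreliable and its confidence intervals can be too wide or too narrow

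*SAP*

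**What the plan says.** SAP section 1.9.2, item 4b, defines the outcome as "Frequency of night awakenings using actigraphy (averaged across the 7-9 day actigraphy period immediately preceding the lab visit". Section 2.6.2.3 repeats the definition ("measured as the average number of night awakenings over the week-long actigraphy period") but calls the variable a highly skewed count.

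The model family is fixed in advance as zero-inflated: "The distribution of night awakenings will be examined to determine which zero-inflated regression model would be most appropriate". Inspection of the data decides only which member of that family to use: "if count data is overdispersed, a negative binomial model may be used instead of a Poisson regression model". The result is to be given as follows: "Incidence rate ratios (IRRs) will be reported with 95% CIs". No p-values are planned. The section names no exposure or offset and no robust variance, and it does not say whether the rate ratio comes from the count part alone.

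The number of nights behind each average varies. Section 2.8.3 says "parents will be asked to fit actigraphy watches to their infant's ankle over a 7-9 day period", and section 2.9.1 sets the lower limit: "Actigraph data for each participant will be excluded from all analysis if there are < 3 days day or night data". Section 2.8.3 adds, for missing actigraphy data, "we may prorate if data is available from 70% of the home assessment period", with missing values replaced by the child's own mean.

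**The concern.** Poisson and negative binomial likelihoods describe integers whose variance is at least the mean. An average over several nights is mostly non-integer, and its sampling variance is well below its mean. Two things follow. The overdispersion check, which decides between the two models, is made on a scale where overdispersion has been averaged away. The model-based standard error also rests on a variance that the data do not have.

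Zero inflation is a separate weakness. An average is zero only when every valid night was zero, so there may be almost no zero class to model. Where there is one, the count-part rate ratio need not be the ratio of mean awakenings between arms.

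With no p-values, the ratio and its CI carry the planned between-arm information on this outcome. Section 2.6.2.1 says of the continuous outcomes that effect estimates are there to illustrate the size of effects. For night awakenings, an interval of the wrong width does that badly.

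**Working it through.** The SAP gives no awakening rate, between-child variance or zero share, so there is no figure of its own to reproduce. Inputs from the SAP are the averaged outcome (1.9.2, 2.6.2.3), 3 to 9 nights (2.8.3, 2.9.1) and 35 randomised per arm (1.8). Assumed inputs are nightly Poisson counts with mean m, between-child gamma variation with squared CV d, K valid nights uniform on 3 to 9, 30 analysed children per arm and a true ratio of 0.75.

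**1. The overdispersion check.** For a total T over K nights:

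- Var(T)/mean(T) = 1 + K·d·m
- Var(T/K)/mean(T/K) = (1/K) × Var(T)/mean(T)

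With m = 2, CV = 0.5 (d = 0.25) and K = 7:

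- Total: mean 14, variance 14 + 0.25 × 14² = 63, ratio 4.5.
- Average: mean 2, variance 2/7 + 0.25 × 2² = 1.29, ratio 0.64 (= 4.5/7).

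The same children look underdispersed on one scale and clearly overdispersed on the other. With 7 nights, the average looks overdispersed only once the total's variance exceeds 7 times its mean.

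**2. Width of the CI.** With n per arm and arm means m0 and m1, the log ratio has:

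- SE assumed by Poisson on the average: √[(1/m0 + 1/m1)/n]
- true SE: √[(E(1/K)(1/m0 + 1/m1) + 2d)/n]

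Here E(1/K) = (1/3 + 1/4 + … + 1/9)/7 = 0.190. The sample size cancels from the ratio of the two. If d = 0, that ratio is 1/√0.190 = 2.30 at every rate.

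Worked case, m0 = 10, m1 = 7.5, d = 0.25: assumed SE √(0.2333/30) = 0.088; true SE √[(0.190 × 0.2333 + 0.5)/30] = 0.135; ratio 0.65.

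Coverage is simulated (300 to 1000 runs per scenario). ZIP is zero-inflated Poisson and NB is negative binomial, all fitted to the average with no offset and model-based SE.

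| Mean per night (m0) | d | Poisson SE / true SE | Poisson | ZIP | NB |
|---|---|---|---|---|---|
| 1 | 0 | 2.30 | about 1.00 | about 1.00 | 1.00 |
| 1 | 0.25 | 1.57 | 1.00 | 1.00 | 1.00 |
| 3 | 0.25 | 1.10 | 0.96 | 0.98 | 0.97 |
| 10 | 0.25 | 0.65 | 0.79 | 0.80 | 0.93 |
| 1 | 1 | 0.98 | 0.94 | – | 0.96 |
| 3 | 1 | 0.60 | 0.78 | – | 0.93 |
| 10 | 1 | 0.34 | 0.51 | – | 0.91 |

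Negative binomial corrects the too-narrow side. It cannot correct the too-wide side, because its variance cannot fall below the mean.

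**3. Bias from the absent offset.** Without an offset, the estimated ratio was about 0.74 to 0.76 against a true 0.75. The average is already per night, so no bias arises.

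**4. Zero inflation.** Under Poisson with 7 nights, P(no awakening) = exp(−7m): 3.0% at m = 0.5 and 0.09% at m = 1. Between-child variation raises this: (1 + 7dm)^(−1/d) gives 8.1% at m = 0.5, d = 0.25. A negative binomial already produces those zeros without an inflation part.

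With structural-zero shares p0 and p1, the ratio of arm means is IRR × (1 − p1)/(1 − p0). If p0 = p1, the two ratios are equal. If p0 = 0.1, p1 = 0.3 and IRR = 0.75, the ratio of means is 0.75 × 0.7/0.9 = 0.583. ZIP on the average then reported 0.59 at mean 1, 0.61 to 0.68 at mean 3 and 0.75 at mean 10. In the last case its CI covered 0.583 in only 14% of runs.

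**5. The alternative.** Totals with a log(nights) offset gave coverage of 0.92 to 0.97 with negative binomial and 0.92 to 0.95 with Poisson and robust SE. An offset alone is not enough: ZIP on totals with model-based SE gave 0.785, 0.615 and 0.39 at means 1, 3 and 10 (d = 0.25).

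**The case against.** Four points count against a stronger reading.

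- A reader might infer that the missing exposure term distorts the ratio. It does not (step 3), and the SAP is silent on an offset rather than excluding one.
- A reader might infer that the reported rate ratio is not the ratio of awakenings between arms. That holds only if structural-zero shares differ between arms, and nothing in the SAP suggests that they will. If all-zero children are rare, the inflation part has little to act on and the two ratios nearly agree.
- A reader might infer that the CIs are wrong in every case. The plan allows negative binomial, which is near nominal at 3 to 10 awakenings per night with between-child variation (0.91 to 0.97). Where it fails, it errs towards intervals that are too wide. This defence is incomplete: the plan says only that it may be used, and on the averaged scale the trigger for using it can fail to fire (step 1).
- The stakes are limited. Outcome 4b is one sub-item. It is absent from the traffic-light criteria in section 2.4 and from the outcomes named in section 1.1.1 for powering a later trial. Section 2.6.1 also summarises it descriptively, section 2.11 leaves room for seemingly unrelated regression, and section 2.12.1 labels between-arm differences preliminary and underpowered.

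These points limit the consequences. They do not remove the mismatch between an averaged outcome and a count likelihood.

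**Conclusion.** The point holds in a conditional form. Section 2.6.2.3 gives a count likelihood to an average, and the overdispersion check is unreliable on that scale by a factor equal to the number of nights. That part is algebra and depends only on averaging.

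The size of the CI error depends on assumed rates and variances. Intervals are about 2.3 times too wide with no between-child variation and still about 1.6 times too wide at 1 per night with d = 0.25. Poisson-type intervals are too narrow at high rates with variation, with coverage down to 0.79 at mean 10, d = 0.25, and 0.51 at d = 1. Negative binomial is near nominal at higher rates with variation, but too wide at low rates with little variation.

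Fixing zero inflation in advance has no stated basis, and it alters the meaning of the ratio only if structural zeros differ by arm. The impact is modest, and the rewrite is worth making because it is cheap.

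**What to change.** Rewrite section 2.6.2.3 along these lines:

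- The dependent variable is each child's total awakenings over observed valid nights, analysed by negative binomial or Poisson regression with log(observed valid nights) as offset and robust standard errors.
- Report the ratio of awakenings per night between arms with its 95% CI.
- Nights filled in under section 2.8.3 count neither in the total nor in the exposure. Replacing a missing night by the child's own mean leaves the average unchanged but would overstate the nights observed.
- Drop zero inflation as the default. Use it only if the totals show more zeros than the chosen model reproduces, and then report the ratio of overall arm means, not the count-part ratio alone.
- Judge overdispersion on the totals. With robust standard errors, little hangs on that choice.

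The per-night average in section 1.9.2 can stay as the descriptive summary. The cost is one paragraph of SAP wording. No new data are needed, since totals and valid nights are already required to form the average and to apply the three-night minimum. The analysis extract must carry the number of valid nights per child.
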